## Study Summary

|                                |                                                                                                                                                                                                                                                                                                                                                                                                                                                                                                                                                                                                                                                                                                                                                                                                                    |
|--------------------------------|--------------------------------------------------------------------------------------------------------------------------------------------------------------------------------------------------------------------------------------------------------------------------------------------------------------------------------------------------------------------------------------------------------------------------------------------------------------------------------------------------------------------------------------------------------------------------------------------------------------------------------------------------------------------------------------------------------------------------------------------------------------------------------------------------------------------|
| Study Purpose           | To evaluate the effect of topical diclofenac on clinical outcomes of chronic Achilles tendinopathy (CAT).                                                                                                                                                                                                                                                                                                                                                                                                                                                                                                                                                                                                                                                                                                          |
| Study Design            | Placebo controlled trial with random allocation.                                                                                                                                                                                                                                                                                                                                                                                                                                                                                                                                                                                                                                                                                                                                                                   |
| Aims                    | 
Primary: To determine whether topical diclofenac affects clinical outcome after 4 weeks of treatment (VISA-A score).
 
Secondary: To determine if topical diclofenac changes pain, pain threshold, or mechanical properties of the Achilles tendon in subjects with chronic Achilles tendinopathy.
                                                                                                                                                                                                                                                                                                                                                                                                                                                                                       |
| Hypothesis              | Individuals treated with topical diclofenac will have a greater improvement in VISA-A score at 4 weeks than those treated with placebo gel.                                                                                                                                                                                                                                                                                                                                                                                                                                                                                                                                                                                                                                                                        |
| Sample Size             | 100 subjects                                                                                                                                                                                                                                                                                                                                                                                                                                                                                                                                                                                                                                                                                                                                                                                                       |
| Study Location          | Vancouver, Alan McGavin Sports Medicine UBC, and [name] practice ([name]).                                                                                                                                                                                                                                                                                                                                                                                                                                                                                                                                                                                                                                                                                                       |
| Main Inclusion Criteria | 
Study Sample: Male and female subjects aged 19 years and older; fluent in English; subject diagnosed with Achilles tendinopathy (unilateral or bilateral; midportion or insertional) by a health care professional; symptoms for 3 months or more; subjects who are able to give informed consent; VISA-A score less than 80; Subjects who are engaged in an active rehabilitation program prescribed by an exercise specialist.
                                                                                                                                                                                                                                                                                                                                                                     |
| Main Exclusion Criteria | 
Study Sample: Male and female subjects aged 18 years and younger; subjects with a BMI greater than 30.0; subjects with previous Achilles tendon rupture (complete or partial); subjects diagnosed with chronic pain syndrome, diabetes, or systemic inflammatory disease; subjects with a history of gastric ulcers, kidney disease or unstable hypertension; subjects with symptomatic osteoarthritis of the spine or lower extremities; subjects who have received corticosteroid injections in the Achilles region; subjects who take non-steroidal anti-inflammatory medication regularly; subjects who have been prescribed anticoagulants or fluroquinolones within the past 5 months; subjects with allergies to diclofenac or placebo gel; subjects who are unable to give informed consent.
 |
| Intervention            | Topical 10% diclofenac, 1g massaged into tendon TID x 4 weeks vs placebo.                                                                                                                                                                                                                                                                                                                                                                                                                                                                                                                                                                                                                                                                                                                                          |
| Primary Outcome         | VISA-A score (4 weeks)                                                                                                                                                                                                                                                                                                                                                                                                                                                                                                                                                                                                                                                                                                                                                                                             |
| Secondary Outcomes      | 1. Pain (Numeric Pain Rating Scale, 0 - 10)                                                                                                                                                                                                                                                                                                                                                                                                                                                                                                                                                                                                                                                                                                                                                                        |

- i. Average pain during all tendon loading activities over last week
  - ii. Average pain during rehabilitative exercise over last week
  - iii. Average pain at rest during last week
  - iv. Current resting pain
2. Patient-reported change in symptoms (7 point scale from substantially better to substantially worse)
  3. Pressure pain threshold (N) and tendon stiffness (N/m)

## 1. Introduction

Chronic Achilles tendinopathy, a painful condition, is prevalent in the general population yet no program has been developed which can successfully treat this disorder in all cases. Recent evidence has shown that pain may be a limiting factor in a person's ability to rehabilitate their Achilles tendon. In order to help researchers develop a more effective rehabilitation program for tendinopathies, we will investigate the effects of topical diclofenac on individuals with CAT.

## 2. Background

Chronic Achilles tendinopathy (CAT) is a clinical condition characterized by a breakdown of collagen fibres, increased vasculature, and an increase of non-collagenous matrix in the Achilles tendon. The Achilles tendon is an amalgamation of the gastrocnemius and soleus which inserts at the calcaneus and is the largest tendon in the body. Chronic Achilles tendinopathy often occurs as an overuse injury due to a failure in the body's healing response following repetitive tendon overloading. CAT is a common injury in athletes that participate in sports that involve running and jumping but the condition has also been found in overweight sedentary middle-aged adults. The cause and pathogenesis of chronic Achilles tendinopathy are likely to be diverse and multifactorial in many cases. Mafi et al. (2001) believes that age, sex, body composition, and ankle instability are predisposing factors that increase the odds of developing the chronic condition.

The main symptom associated with chronic Achilles tendinopathy is pain within the mid portion or insertion site of the tendon. Other symptoms include impaired performance, stiffness, and swelling. Dissimilar to acute Achilles tendinopathy, there is much less inflammation or biochemical inflammation mediator, prostaglandin E2, present within the Achilles tendon. Recent studies have shown that there may be some inflammation in the connective tissue surrounding the tendon. The exact mechanisms that cause the pain associated with CAT remain uncertain. Initially, it was hypothesized that the pain was due to an inflammation-repair response to overuse injury of the Achilles tendon. Alfredson et al. (1999) used a micro-dialysis technique to compare the biochemical concentrations of prostaglandin E2 in normal tendons to

chronic tendinopathic Achilles tendons. The authors found that there was no significant difference between the two, although there was a non-significant trend for the injured tendon to display increased prostaglandin E2 levels. They concluded that the pain associated with CAT was not due to inflammation. During the same study, Alfredson et al (1999) found that the excitatory neurotransmitter glutamate was present in higher concentrations within the tendinopathic tendons. Glutamate is known to play a role in both central and peripheral pain regulation with nociceptors, and diclofenac is known to inhibit peripheral glutamate-mediated nociception. Webbron (2008) uses the term neoneuralization to describe the proliferation of sensory nerve endings in response to pro-inflammatory cytokines in damaged tissue. He found that along with the new innervation, substance P, a neurotransmitter that is involved with the transmission of pain within the central nervous system, was much more abundant in tendinopathic tendons when compared to healthy tendons. In a study of rotator cuff disease, the amount of pain was moderately correlated with the amount of substance P in the subacromial bursa. This indicates that substance P may also play a role in pain mechanisms. Diclofenac has recently been shown to inhibit substance P release from sensory neurons. Thus, in addition to reducing the levels of classic inflammatory substances like prostaglandin E2 within the painful tendon, diclofenac could inhibit other relevant nociceptive mechanisms.

Exercise, in addition to its ability to maintain healthy tissue, can be used as a treatment for tissue repair and adaptation. Mechanotransduction is the process in which a cellular signal cascade is created in response to mechanical stimuli and promotes structural change within those or surrounding cells. This process occurs during exercise. Fahlstrom et al. (2003) found that an eccentric calf training program done twice a day for 12-weeks at the maximum tolerable intensity (Alfredson protocol) was clinically significant in reducing the symptoms in subjects with CAT. Eccentric exercise may increase tendon tensile strength and volume by altering the production of type 1 collagen. Heavy, painful eccentric exercise has produced clinically significant results for rehabilitation although it is less effective in non-athletes and older adults. Silbernagel et al. (2007) found that there were no negative effects from allowing individual with CAT to continue Achilles tendon loading activities (i.e. sports) while using a pain-monitoring model to guide their level of therapeutic exercise and recreational activities. Thus, exercise appears to be a safe treatment for people with tendinopathy, who are mainly limited by the experience of pain.

Diclofenac is a non-steroidal anti-inflammatory drug (NSAID) that works by preventing an enzyme, cyclooxygenase (COX), from making prostaglandins. Diclofenac also has analgesic effects which are the topic of ongoing investigations. At high tissue concentration diclofenac can block sodium channels and prevent nociceptive afferent fibers from firing action potentials. Diclofenac has been shown to minimize the pain associated with osteoarthritis and chronic lateral epicondylitis. A Cochrane review written by Pattanittum et al (2013) evaluated 5 studies that focused on the comparison NSAIDs and placebos on elbow tendon pain due to tendinopathy. The review concluded that topical NSAIDs were more effective than the placebo for short time periods (up to 4 weeks) but questioned the methodological rigour of the studies

performed. A crossover randomized study performed by Burnham et al (1998) evaluated the effectiveness of topical diclofenac for chronic lateral epicondylitis. He found that with the use of topical diclofenac (3 times a day for a week) subjects had a significant reduction of pain and wrist extensor weakness. Many studies have investigated the use of diclofenac with chronic elbow tendinopathy, however there is no current literature to our knowledge that investigates the use of diclofenac with chronic Achilles tendinopathy. Our own group recently conducted a pilot study (short-term, cross-over placebo controlled trial) which found that 10% diclofenac significantly reduced the pain associated with Achilles tendinopathy, and improved people's ability to generate force through the Achilles tendon.

## **2.1 Significance**

This study can help contribute to the development of a possible adjunct treatment to reduce pain and improve Achilles tendon function among individuals with CAT.

## **3. Aims of Study**

1. To determine whether a 4-week course of 10% topical diclofenac improves clinical outcome (VISA-A score) relative to placebo.
2. To determine whether any improvements seen with diclofenac compared to placebo persist 8 weeks later (i.e. 12 weeks from baseline)

## **4. Objective**

The objective of this study is to evaluate the effects of topical diclofenac on the pain and impairment (VISA-A score) associated with chronic Achilles tendinopathy.

## **5. Hypothesis**

Individuals treated with topical diclofenac will have a greater improvement in VISA-A score at 4 weeks than those treated with placebo gel.

## **6. Study Design**

Placebo-controlled trial, random allocation in a 1:1 ratio.

## **7. Study Location**

This study will be conducted at Fortius Sport and Health, Burnaby, Vancouver, Alan McGavin Sports Medicine UBC, and [name] practice ([name]).

## **8. Study Population**

One hundred Vancouver community dwelling participants will be recruited from sporting clubs, running groups, gyms, community centres, running trails, and the Fortius and Alan McGavin Sports Medicine Centres and [name] practice by health professionals' recommendations and posters.

## **9. Eligibility Criteria**

### **Inclusion Criteria**

1. Male and female subjects aged 19 years and older.
2. Fluent in English.
3. Subjects previously diagnosed with Achilles tendinopathy by a health care professional (imaging at the discretion of the treating physician) and demonstrating the following criteria – localized tendon pain and thickening, worsened with palpation and tendon loading activities, and no clinical suspicion of other diagnoses.
4. Symptoms for 3 months or more.
5. Subjects who are able to give informed consent.
6. VISA-A score less than 80.
7. Subjects who are engaged in an active rehabilitation program prescribed by an exercise specialist

### **Exclusion Criteria**

1. Male and female subjects aged 18 years and younger.
2. Subjects with a BMI greater than 30.0.
3. Subjects with previous Achilles tendon rupture (complete or partial).
5. Subjects diagnosed with chronic pain syndrome, diabetes, hyperprproteinemia, metabolic syndrome, or systemic inflammatory diseases.
6. Subjects with a history of gastric ulcers, kidney disease or unstable hypertension.
7. Subjects with symptomatic osteoarthritis of the spine or lower extremities.
8. Subjects who have received corticosteroid injections in the Achilles region.
9. Subjects who take non-steroidal anti-inflammatory medication regularly.

10. Subjects who have been prescribed anticoagulants or fluroquinolones within the past 5 months.

11. Subjects with allergies to diclofenac or placebo cream.

12. Subjects who are unable to give informed consent.

## **10. Study Outcomes**

### **10.1 Primary Outcome**

VISA-A score (0-100) at 4 weeks.

### **10.2 Secondary Outcomes**

1. Pain (Numeric Pain Rating Scale, 0 - 10)

- i. Average pain during all tendon loading activities over last week
- ii. Average pain during rehabilitative exercise over last week
- iii. Average pain at rest during last week
- iv. Current resting pain

2. Patient-reported change in symptoms (7 point scale from substantially better to substantially worse)

3. Pressure pain threshold (N) and transverse tendon stiffness (N/m) measured over the site of maximum tendon stiffness

## **11. Study Procedures**

### **11.1 Recruitment and Screening**

Subjects will be recruited by placing posters in sporting clubs, running groups, gyms, community centres, running trails, and medical clinics, or by running advertisements in local newspapers or websites. Once contacted, a telephone or email screen will be conducted to review minimal eligibility criteria and explain the purpose of the study. They will be advised that participants should receive no new treatment throughout the study, and to not make any changes to treatment they might already be receiving. If minimal criteria are met and the participant is interested in joining the study, a consent form will be emailed and a first study visit will be booked. The potential participants will be instructed to not do any moderate to vigorous physical activity 72 hours prior to Visit 1, and to refrain from taking any NSAIDS for 1 week (no analgesics for 24hrs).

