## **Visit 1 – Week 0**

Consent will be obtained by [name]. EB will complete the eligibility screen, which includes data collection (demographic information, BMI, rehabilitation history, and medical questionnaire including date of last NSAID taken). Subjects will complete the VISA-A questionnaire (a self-report questionnaire which measures Achilles tendinopathy severity). The investigator will use the MyotonPro to assess the transverse tendon stiffness at the location of maximal tendon thickening, and will use the AlgoMed Algometer to assess the subject's pain pressure threshold (PPT) on the most affected area of the Achilles tendon. Testing will be conducted at a controlled rate (30 KPa/s) with the subject lying prone on a treatment plinth. Pressure is gradually applied until the subject first experiences onset of pain, at which point they push a button. In rare cases where the person with CAT has baseline (resting) pain, then they will be instructed to press the button at the first increase in pain.

Subjects will then be issued with either placebo or 10% diclofenac gel. The gel will be supplied by a pharmacist, and the investigator and subject will not know the identity of the tubes. Subjects will be instructed to massage 1 gm of gel on the most painful area of the tendon for 30 - 45 seconds. The subject will also be instructed to how often to apply the gel (every 8 hours/3 times a day for 4 weeks) before the next scheduled appointment. They will be asked to complete a medication administration diary to confirm their compliance with the regimen, to document any medical or paramedical treatments received, and an exercise diary to record their exercise and physical activities.

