## **Check-ins**

The participants will be contacted twice by phone or email during weeks 1 and 3. The investigator will inquire about tolerability of the treatment and any side-effects, and remind the participant to keep filling out the diaries.

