## **Visit 2**

The second appointment will be scheduled 4 weeks following the initial appointment (within a 5 day margin of error). At the start of the second visit, subjects will be asked which treatment they thought they received, any remaining gel and the study diaries will be collected from the subject, and the outcome measures will be taken (VISA-A, pain, global improvement, non-protocol treatments, side effects, pain pressure threshold, tendon stiffness, returned to pre-injury activity level with no or minimal pain?).

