#### AlgoMed Algometer

The Algometer is a computerized pressure meter used to assess tissue pain perception in muscle pain syndromes. The device is set to a specific pressure (KPa) and placed on the site of maximal Achilles tendon pain. The subject's response to pressure threshold and tolerance tests are then processed by software and graphed on the computer for analysis. The subject will lie face down on a treatment plinth for the PPT measurement. The subject presses a button the moment they first begin to perceive pain, and the test is stopped and the pressure value recorded. The same site will be tested on both occasions.

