## **12. Statistical Considerations and Data Analysis**

The pain pressure threshold measurement will be repeated three times and the two closest measures will be used for analysis. To avoid wind up, we will wait one minute between each measure.

A repeat measures ANOVA will be used to detect the effect of time (0, 4, 12 weeks) or treatment (placebo vs active) on VISA-A score. Paired t-tests will be used to detect changes in pain, pain pressure threshold and tendon stiffness from baseline to 4 weeks. The proportion of individuals who have returned to full activity at the different timepoints will be reported as point estimates with 95% confidence intervals. The global rating of change (Likert scale) will be compared between groups using a Mann Whitney-U test.

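### Activity, NSAID and analgesic restrictions are specified before Visit 1 but not before Visit 2, so the paired 4-week changes in pressure pain threshold and tendon stiffness need not be measured under like conditions (secondary outcomes, low severity)

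*Protocol*

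**What the plan says.** Protocol section 11.1 (Recruitment and Screening) tells potential participants to "not do any moderate to vigorous physical activity 72 hours prior to Visit 1, and to refrain from taking any NSAIDS for 1 week"; the same sentence adds 24 hours without analgesics. At Visit 1 the date of the last NSAID is recorded, and PPT and transverse tendon stiffness are measured.

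The contacts before the second measurement carry no such instruction. Under Check-ins, "The participants will be contacted twice by phone or email during weeks 1 and 3", to ask about tolerability and side effects and to prompt diary completion. Under Visit 2, only the timing and the measurements are fixed. The algometer description standardises one aspect across visits: "The same site will be tested on both occasions". It says nothing about preparation.

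Section 12 then states: "Paired t-tests will be used to detect changes in pain, pain pressure threshold and tendon stiffness from baseline to 4 weeks".

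Some cover exists:
- Section 11.1 advises that "participants should receive no new treatment throughout the study, and to not make any changes to treatment they might already be receiving".
- Section 9 excludes regular NSAID users.
- At Visit 1 participants receive a medication diary, which also documents treatments received, and "an exercise diary to record their exercise and physical activities".
- At Visit 2, "any remaining gel and the study diaries will be collected from the subject", and non-protocol treatments are recorded.

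**The concern.** A paired change is interpretable when the two measurements differ in time and treatment and in little else. Here the baseline is taken after prescribed rest and drug washout, and the follow-up has no stated preparation. All participants must be in an active rehabilitation programme (section 9), so loading shortly before Visit 2 is to be expected. Occasional analgesic use that predates the trial may continue without breaching the advice in section 11.1.

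PPT is a pain measure and could respond to recent analgesia. PPT and stiffness could both respond to recent loading. The protocol evidently thought these influences worth controlling at entry. At stake is how the planned paired tests read: a significant change could partly reflect the end of the pre-visit restrictions, and a real change could be partly hidden. Because preparation is a visit procedure, an analysis plan could not restore it afterwards.

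**Working it through.** **1. The provisions side by side**

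| Condition | Before Visit 1 | Before Visit 2 |
|---|---|---|
| Moderate to vigorous activity | None for 72 hours (11.1) | Not specified |
| NSAIDs | None for 1 week (11.1) | Not specified |
| Analgesics | None for 24 hours (11.1) | Not specified |
| Check of drug use | Date of last NSAID | Diaries; non-protocol treatments |
| PPT site | Most affected area | Same site |

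The NSAID clause does not itself name a visit. It stands in the pre-Visit 1 instruction to potential participants, and it cannot sensibly be read as covering the treatment period without an exemption for the diclofenac gel.

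**2. The plan's own figure**

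The sample size section assumes a difference of 15 − 5 = 10 VISA-A points, SD 17, two-sided alpha 0.05 and power 0.80. By the normal formula, n = 2 × (1.960 + 0.842)² × 17² / 10² = 45.4, rounded up to 46 per group, as stated. This concerns VISA-A and is not affected by the present point. The documents give no SD for PPT or stiffness and no size for an activity or analgesic effect, so everything below is illustration with assumed inputs.

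**3. Within-arm paired test (the type of test planned)**

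Let b be the shift due to preparation alone, in SDs of the paired change. With no true change, the rejection rate at two-sided 0.05 comes from a noncentral t with noncentrality b × √n and n − 1 degrees of freedom. I use n = 46 (stated requirement) and n = 100 / 2 = 50 (planned total, 1:1).

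| Assumed b | n = 46 | n = 50 |
|---|---|---|
| 0 | 5% | 5% |
| 0.1 | 10% | 11% |
| 0.2 | 26% | 28% |
| 0.3 | 51% | 55% |
| 0.5 | 91% | 93% |

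**4. Between-arm contrast (not the test named for these outcomes)**

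Bias = (difference between arms in the share affected) × (shift per affected participant). The noncentrality is d × √(n/2) = 5d at n = 50, with 98 degrees of freedom. A true effect of 0.566 SD gives 80% power. The power column takes the bias to dilute that effect.

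| Share difference × shift | Bias (SD) | Rejection, no drug effect | Power if diluted |
|---|---|---|---|
| 0 × any | 0 | 5.0% | 80% |
| 0.10 × 0.2 | 0.02 | 5.1% | 77% |
| 0.10 × 0.5 | 0.05 | 5.7% | 72% |
| 0.20 × 0.5 | 0.10 | 7.9% | 64% |

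The within-arm change is directly exposed. The between-arm contrast is exposed only through a difference by arm, and then modestly over this range.

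**The case against.** Four arguments deserve weight.

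*Silence is not difference.* A reader might infer that the 4-week measurements are in fact taken under other conditions than baseline. The documents do not say so. They leave preparation for Visit 2 open, and a site might well repeat the instruction. What stands is that nothing requires it.

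*The drug gap is partly covered.* Someone who starts a new analgesic before Visit 2 departs from the advice in section 11.1, and regular NSAID users are excluded. That is right. What remains open is continued occasional use, together with physical activity.

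*The asymmetry may be deliberate.* The restrictions sit under screening, and measuring at 4 weeks under usual rehabilitation is defensible. One secondary outcome is "Average pain during rehabilitative exercise over last week", and a 72-hour pause would take up to three of its seven recall days, just before the primary VISA-A. This argument largely stands for activity, although the same pause already precedes the baseline VISA-A. It has little force for a drug washout.

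*Randomisation and blinding protect the comparison.* A reader might infer that the drug-placebo contrast is biased. The documents do not support that: allocation is random 1:1, investigator and participant do not know the tubes' identity, and a common shift cancels. A difference in rescue use is conceivable if the drug relieves pain, and more analgesia on placebo would dilute an effect on PPT. No rate is given, and differing activity could act in another direction.

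It is also true that matched preparation would not turn a within-arm paired test into a test of the drug. That is a separate matter.

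**Conclusion.** The point holds as a low-severity gap in the visit procedures for secondary outcomes. Preparation is prescribed for the baseline and left unspecified for the 4-week measurement paired with it. The planned within-arm changes in PPT and stiffness are directly exposed. Between-arm bias is conditional on a difference in analgesia or loading by arm, and its size cannot be derived from the documents. The rates above rest on assumed shifts and shares, and the between-arm figures also on a test that section 12 does not name for these outcomes. They show sensitivity and are not evidence that a bias exists.

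A reader might extend the point to the primary outcome, since VISA-A is also completed at both visits. The documents do not support that: the hypothesis concerns the difference between arms in improvement, from which a common shift drops out, and nothing shows preparation differing by arm. No effect on the primary comparison is claimed.

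**What to change.** Add to Visit 2 the same 1-week NSAID washout (study gel excepted) and 24-hour analgesic washout that precede Visit 1. Give the instruction at Visit 1 and repeat it at the existing week-3 check-in. At both visits record the time of the last NSAID or analgesic, extending the NSAID date already taken at Visit 1, and the time of the last moderate to vigorous activity. Measure participants who did not comply and keep them in the analysis.

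Treat a second 72-hour activity pause as optional, because it interrupts prescribed rehabilitation and overlaps the recall week of the exercise-pain item. If it is not adopted, the recorded time of last activity at least allows the difference to be described.

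The cost is a sentence under Visit 2, a line in the Visit 1 instructions, a reminder at a contact already planned and two items on the visit form. The downside is a small burden on participants and the brief withholding of occasional analgesics.
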